### 2.6. Statistical Design

Cisplatin and doxorubicin will be used in patients with peritoneal carcinomatosis of ovarian and gastric origin and in primary tumors of the peritoneum. A dose escalation model based on a two-agents combination design published by Riviere is adopted [25]. It is an extension of the Continual Reassessment Method in case of two-dimensional dose-escalation, which identifies the MTD of the combination of cisplatin and doxorubicin based on the probability of dose limit toxicity (DLT) of each combination of the two agents.

An empirical logistic model in a Bayesian framework is adopted. The model of the probability of toxicity at a given dose combination is defined as following:*logit*(*π*(*d*_1*j*_,*d*_2*k*_*α*,*β*_1_,*β*_2_,*β*_3_) = *α* + *β*_1_*d*_1,*j*_ + *β*_2_*d*_2,*k*_ + *β*_3_*d*_1,*j*_*d*_2,*k*_(1)
where *β*_1_ represents the toxicity effect of agent 1 (cisplatin), *β*_2_ of agent 2 (doxorubicin), and *β*_3_ is the interaction effect potentially due to the combination of the agents.

For parameters α and *β*_3_, a vague normal prior distribution centered at 0 to indicate that a priori either positive or negative values are favored, letting the observed number of patients with toxicity driving the posteriori distribution. For parameters (*β*_1_, *β*_2_), an exponential distribution with mean 1 is chosen, based on the consideration that (*β*_1_, *β*_2_) should numerically be in a neighborhood of 1.

The working model is defined by dose levels *d*_1*,j*_ for cisplatin and *d**_2,k_* for doxorubicin, which have been identified on the basis of a modified Fibonacci series.

The first cohort of participants will be treated with cisplatin 15 mg/sm body surface in 150 mL NaCl 0.9% and doxorubicin 3 mg/sm (cohort 1); the following cohort will receive CDDP 30 mg/sm and DXR 6 mg/sm (cohort 2) and the third cohort CDDP 50 mg/sm and DXR 10 mg/sm (cohort 3). Dose escalation will be continued by the protocol according to the probability model up to a maximum of CDDP 100 mg/sm (that is the dose currently used in HIPEC procedure) and DXR 30 mg/sm.

The different dose increases will be adopted as reported in Table 1.

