The recommended doses of both agents are those of the dose level combination associated with a probability of DLT closes to the DLT probability target at 25%. An escalation with overdose and under-dose control (for probability of toxicity less than 16% in case of under-dosing; and probability of toxicity greater than 33% in case of overdosing) is further applied. No skipping dose is allowed, nor intra-patient dose escalation.

As a stopping rule, the maximum number of 42 patients is considered.

Oxaliplatin will be used in patients presenting peritoneal carcinomatosis of intestinal origin.

An extension of the Continual Reassessment Method based on a two-parameter probability model proposed by Neuenschwander will be used to identify the recommended dose of oxaliplatin [26].

The first cohort of patients will be treated with oxaliplatin 100 mg/sm body surface in 150 dextrose solution 5% (cohort 1); the following cohort will receive oxaliplatin 135 mg/sm (cohort 2) and 155 mg/sm for the third one (cohort 3).

After each cohort is assessed, a probability of toxicity, given the data observed (i.e., the number of patients who experienced toxicity), is computed on the basis of the following 2-parameters logistic regression model
*logit*(*π*(*d***_j_*;*α*,*β*) = *log**α* + *β* × *d***_j_*, *α*,*β* > 0(2)
where the parameters (*α*, *β*), which are positive valued, ensure a monotonically increasing dose-toxicity relationship; *d***_j_* is a dose standardized to a reference dose, so that log *α* can be interpreted as the log-odds of toxicity when *d**_*i*_ is the reference dose.

Parameters (*α*, *β*) will be calibrated to reflect information about toxicities, corresponding to assuming a toxicity probability of oxaliplatin at the maximum dose of 460 mg equal to 25% and a toxicity probability at the starting dose of 120 mg equal to 10. Calibration of the parameters will be carried out according to the approach proposed in Thall [27], assuming a zero a priori correlation.

An escalation with overdose and under-dose control (for probability of toxicity less than 16% in case of under-dosing; and probability of toxicity greater than 33% in case of overdosing) is further applied. No skipping dose is allowed, nor intra-patient dose escalation.

The dose escalation design of oxaliplatin is presented in Table 2.

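### Doses of cohorts 2 and 3 are stated without condition, which conflicts on its face with model-based escalation under overdose control, chiefly for cisplatin/doxorubicin

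*Protocol article*

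**What the plan says.** All of the text at issue is in Section 2.6 (Statistical Design) of the protocol article.

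**Cisplatin/doxorubicin.** Cohort 1 receives 15/3 mg/sm. After that, "the following cohort will receive CDDP 30 mg/sm and DXR 6 mg/sm (cohort 2) and the third cohort CDDP 50 mg/sm and DXR 10" mg/sm. The next sentence reads "Dose escalation will be continued by the protocol according to the probability model up to a maximum of CDDP 100 mg/sm", with doxorubicin capped at 30 mg/sm. The design is described as a two-agent extension of the Continual Reassessment Method with a target DLT probability of 25%.

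**Oxaliplatin.** Cohort 1 receives 100 mg/sm. After that, "the following cohort will receive oxaliplatin 135 mg/sm (cohort 2) and 155 mg/sm for the third one (cohort 3"). The sentence that follows says: "After each cohort is assessed, a probability of toxicity, given the data observed (i.e., the number of patients who experienced toxicity), is computed" from the two-parameter logistic model.

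**Both regimens.** The control rule is stated once for each regimen: "An escalation with overdose and under-dose control (for probability of toxicity less than 16% in case of under-dosing; and probability of toxicity greater than 33"%. Neither statement exempts the early cohorts. Dose skipping and intra-patient escalation are both barred. The Abstract calls the whole dose-escalation design model-based.

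**The concern.** In a model-driven design the starting dose can be fixed, and so can the list of dose levels. The dose of a numbered cohort after the first cannot be known in advance, because it depends on the DLTs seen so far. Section 2.6 nevertheless assigns doses to cohorts by number, for cohorts 2 and 3 of each regimen. For cisplatin/doxorubicin it then introduces the model as the means by which escalation goes on, which suggests that the model takes over only after cohort 3.

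At stake is whether DLTs in cohorts 1 and 2 can influence the dose given to the next patients. The least information is available at these moves, and for cisplatin/doxorubicin the relative steps are at their largest. Section 1.3 reports 10.5/2.1 mg/sm as the dose set by the only earlier phase 1 escalation of this combination. Cohort 1 is 15/10.5 = 3/2.1 = 1.43 times that dose, and cohort 3 is 50/10.5 = 10/2.1 = 4.76 times. The unclear instruction therefore covers doses beyond the earlier escalation that the article cites.

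**Working it through.** The article states no figure to reproduce here, so the check compares the passages and then looks at the step sizes.

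**1. The passages side by side**

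| | Cisplatin/doxorubicin | Oxaliplatin |
|---|---|---|
| Doses of cohorts 2 and 3 | 30/6, then 50/10 mg/sm, no condition | 135, then 155 mg/sm, no condition |
| Where the model enters | After cohort 3 is described: "Dose escalation will be continued by the protocol according to the probability model" | Directly after the doses: "After each cohort is assessed, a probability of toxicity, given the data observed" |
| Overdose control | Applied, no exemption | Applied, no exemption |
| Which instruction prevails after excess DLTs | Not said | Not said, but the per-cohort computation points to the model |

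The bar on skipping doses does not settle the matter. It limits upward jumps and does not say whether a cohort may be held or moved down.

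**2. Step sizes, from Tables 1 and 2** (next level / current level − 1)

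- Cisplatin: 30/15 = +100%, 50/30 = +67%, then +34%, +31%, +6%, +8%.
- Doxorubicin: 6/3 = +100%, 10/6 = +67%, then +30%, +38%, +28%, +30%.
- Oxaliplatin: 135/100 = +35%, 155/135 = +14.8%, then +16.1%, +11.1%, +17.5%, +14.9%, +11.1%.

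For cisplatin/doxorubicin the two moves in question are the two largest, with a cumulative rise of 50/15 = 10/3 = 3.33-fold. For oxaliplatin only the first move is the largest. The second ranks fifth of seven, and the cumulative rise is 155/100 = 1.55-fold.

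**3. Could the two instructions diverge in practice?** This is an illustration only. The article gives no cohort size, so 3 and 6 are assumed. It gives no posterior cut-off for the overdose rule, so a simple Beta prior at a single dose level stands in for the article's logistic models.

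Chance of a high DLT count in one cohort. For size 3, P(at least 2 of 3) = 3p²(1 − p) + p³; for size 6 the figure is the binomial tail P(at least 4 of 6).

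| True DLT rate p | At least 2 of 3 | At least 4 of 6 |
|---|---|---|
| 0.25 | 0.156 | 0.038 |
| 0.33 | 0.255 | 0.097 |
| 0.40 | 0.352 | 0.179 |
| 0.50 | 0.500 | 0.344 |

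Posterior probability that the DLT rate exceeds 33% after x DLTs in m patients. A Beta(a, a) prior gives Beta(a + x, a + m − x).

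| Result | a = 1 | a = 0.5 |
|---|---|---|
| 2 of 3 | 0.892 | 0.889 |
| 3 of 3 | 0.988 | 0.993 |
| 4 of 6 | 0.957 | 0.956 |

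Results of this kind are not remote if the true rate is at or above the overdose limit. After them, overdose control would normally weigh against a step up, whereas the listed sequence taken literally steps up.

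**The case against.** The strongest defence is that a consistent reading exists. The listed doses are exactly levels 1 to 3 of Tables 1 and 2. With skipping barred, they describe the planned upward path through those levels, to be followed if the model allows each step. On this reading, the sentence about continuing escalation means that the same model-led process goes on, and overdose control, which has no exemption, covers every move. This reading is possible, so the text does not prove that the design is non-adaptive. But the reader has to supply it: the wording numbers cohorts rather than levels and attaches no condition.

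The defence is much stronger for oxaliplatin. No sentence there defers the model, and the sentence directly after the listed doses says that the probability is computed after each cohort. That sentence belongs to the oxaliplatin text only and cannot be carried over to cisplatin/doxorubicin.

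A reader might infer that the first three cohorts are escalated whatever toxicity is seen. The article does not say this. A reader might also infer that adaptive allocation is lost. That goes too far as well: cohorts 2 and 3 together would be 2 × 3 = 6, or 2 × 6 = 12, of at most 42 cisplatin/doxorubicin patients under the assumed cohort sizes, and later allocation remains model-based.

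The article is also a condensed account of protocol version 3.0, which is not shown and may give the cohort decision rule. That would settle which reading is right, but it would not remove the conflict between the statements printed in the article.

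**Conclusion.** The point holds as a conflict between stated instructions, most clearly for cisplatin/doxorubicin. The doses of cohorts 2 and 3 are written as settled and the model is brought in to continue from there, yet model-based escalation and overdose control are stated without exception. After excess DLTs in cohort 1 or 2 these can lead to different next doses, and nothing says which prevails. The moves affected are +100% and +67%, the largest relative steps in Table 1. For oxaliplatin the same unconditional wording appears, but the conflict is weaker.

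The comparison of passages and the step sizes rest on the article alone. The probabilities in the illustration rest on assumed cohort sizes, assumed DLT rates and a stand-in prior. They show that the instructions can diverge, not how often they would or how many extra DLTs would follow. That size cannot be determined from the article. Because the ambiguity bears on whether observed toxicity can affect the next patients' dose, it should be resolved and not left to interpretation.

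**What to change.** Reconcile the cisplatin/doxorubicin and oxaliplatin parts of Section 2.6 so that, in each regimen, a single stated rule governs the moves from cohort 1 to 2 and from 2 to 3, and so that the listed cohort doses, the model update and the overdose control agree with that rule. The sponsor should take the rule from the full protocol if it is given there. Which rule applies is for the sponsor and investigators to state; no dose or escalation rule is proposed here.

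The cost is about one sentence per regimen. If the full protocol carries the same wording, it needs a corresponding clarification.

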## Abstract

Pressurized Intra-Peritoneal Aerosol Chemotherapy (PIPAC) is a novel laparoscopic intraperitoneal chemotherapy approach offered in selected patients affected by non-resectable peritoneal carcinomatosis. Drugs doses currently established for nebulization are very low: oxaliplatin (OXA) 120 mg/sm, cisplatin (CDDP) 10.5 mg/sm and doxorubicin (DXR) 2.1 mg/sm. A model-based approach for dose-escalation design in a single PIPAC procedure and subsequent dose escalation steps is planned. The starting dose of oxaliplatin is 100 mg/sm with a maximum estimated dose of 300 mg/sm; an escalation with overdose and under-dose control (for probability of toxicity less than 16% in case of under-dosing and probability of toxicity greater than 33% in case of overdosing) will be further applied. Cisplatin is used in association with doxorubicin: A two-dimensional dose-finding design is applied on the basis of the estimated dose limiting toxicity (DLT) at all combinations. The starting doses are 15 mg/sm for cisplatin and 3 mg/sm for doxorubicin. Safety is assessed according to Common Terminology Criteria for Adverse Events (CTCAE version 4.03). Secondary endpoints include radiological response according to Response Evaluation Criteria in Solid Tumor (version 1.1) and pharmacokinetic analyses. This phase I study can provide the scientific basis to maximize the optimal dose of cisplatin, doxorubicin and oxaliplatin applied as PIPAC.

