### 1.3. PIPAC as a Promising Intraperitoneal Chemotherapy Delivery Technique

PIPAC takes advantage of the physical properties of gas and pressure avoiding the pharmacokinetic limitations of IPC [10]: under-pressure application and drug micronization enhance drugs uptake, peritoneal distribution and penetration depth [11,12,13].

Based on animal experimental data, PIPAC has been tested in patients with recurrent peritoneal carcinomatosis: It has been administered alone or after systemic fluorouracil [13,14,15]. Concomitant systemic treatment is possible with most used regimens, considering no systemic chemotherapy for two weeks before and one week after PIPAC procedure.

Two intraperitoneal regimens are used for PIPAC procedures: cisplatin in combination with doxorubicin and oxaliplatin as monotherapy. At least three PIPAC procedures are done at six- to eight-week intervals, but treatment can be pursued depending on disease response and patient tolerance.

So far, the dosages of these drugs have been set at approximately 20% of the dose used in HIPEC. Only one phase 1 study increased the doses of cisplatin and doxorubicin applied as PIPAC, setting them to a dosage still too low—10.5 mg/sm and 2.1 mg/sm, respectively [16]. Similarly, the oxaliplatin dose used for PIPAC has recently been the subject of a dose escalation study reporting that the recommended phase 2 dose should be 120 mg/sm [17].

The feasibility, safety and tolerance of repeated PIPAC treatment are confirmed by retrospective and prospective studies. Limited hepatic and renal toxicity are reported, associated to acceptable local toxicity: nausea and diffuse abdominal pain are the most complained complications. No acute or cumulative renal, gastrointestinal and hepatic toxicity are described [18,19,20]. Furthermore, surgical complications are rare. Whereas no mortality is observed in prospective trials, the mortality in retrospective studies is 2.7% [21].

At least, PIPAC has been shown to be safe regarding occupational health aspects such as operation theatre air contamination with aerosol chemotherapy particles [22].

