## Figures and Tables

**Figure 1 ijerph-18-05656-f001:**
[figure not shown]
Schematic of single-port PIPAC set-up. The nebulizer connected to a standard injector and a laparoscope are inserted through a Quadport+ platform.

**Table 1 ijerph-18-05656-t001:** Cisplatin and doxorubicin dose escalation design.

Level	Cisplatin (CDDP)	Doxorubicin (DXR)
1	15 mg/sm	3 mg/sm
2	30 mg/sm	6 mg/sm
3	50 mg/sm	10 mg/sm
4	67 mg/sm	13 mg/sm
5	88 mg/sm	18 mg/sm
6	93 mg/sm	23 mg/sm
7	100 mg/sm	30 mg/sm

**Table 2 ijerph-18-05656-t002:** Oxaliplatin dose escalation design.

Level	Oxaliplatin (OXA)
1	100 mg/sm
2	135 mg/sm
3	155 mg/sm
4	180 mg/sm
5	200 mg/sm
6	235 mg/sm
7	270 mg/sm
8	300 mg/sm

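### The oxaliplatin prior is calibrated at a labelled start of 120 mg and maximum of 460 mg, but the trial doses run from 100 to 300 mg/sm and no unit conversion reconciles the two pairs

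*Protocol article*

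**What the plan says.** The oxaliplatin part of section 2.6 uses a two-parameter logistic model in which the dose "is a dose standardized to a reference dose". The prior for the two parameters is fixed by two assumed risks: "oxaliplatin at the maximum dose of 460 mg equal to 25% and a toxicity probability at the starting dose of 120 mg equal to 10". The first point is a percentage. The second has no percent sign and is read here as 10%. Both anchor doses are printed in mg, whereas the treatment doses are in mg/sm.

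The same article gives the trial's doses in three places:

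- Abstract: "The starting dose of oxaliplatin is 100 mg/sm with a maximum estimated dose of 300 mg/sm".
- Section 2.6: "The first cohort of patients will be treated with oxaliplatin 100 mg/sm body surface".
- Table 2, captioned "Oxaliplatin dose escalation design": 100, 135, 155, 180, 200, 235, 270 and 300 mg/sm.

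Neither 120 nor 460 is a level of Table 2. The figure 120 mg/sm does occur elsewhere, as a dose from outside this trial. The Abstract says "Drugs doses currently established for nebulization are very low: oxaliplatin (OXA) 120 mg/sm", and section 1.3 reports from an earlier escalation study that "the recommended phase 2 dose should be 120 mg/sm". The figure 460 occurs nowhere else. For cisplatin, by contrast, section 2.6 gives the origin of the ceiling of 100 mg/sm ("that is the dose currently used in HIPEC procedure"), and that ceiling is the top level of Table 1.

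**The concern.** The two anchors are given the names of the first and last doses of the trial, but their values are not those doses. The calibrated parameters enter the toxicity probability computed after each cohort, to which the under-dose (below 16%) and overdose (above 33%) limits are applied. A prior carries most weight while few patients have been observed.

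Two explanations are possible. Either 10% and 25% were meant for the trial's own first and last doses and the prior was set at the wrong ones, or 120 and 460 are reference doses from outside the trial and only their names are wrong. The text does not let a reader decide between them, and it does not settle the unit. The prior therefore cannot be reproduced or checked against Table 2.

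**Working it through.** **Inputs.** Anchors (section 2.6): 10% at 120 and 25% at 460. Trial doses (Abstract, section 2.6, Table 2): 100 to 300 mg/sm. Body surface area is not given, so 1.5 to 1.9 sm is assumed where it is needed.

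**Step 1: can a unit explain the difference?** A change of unit leaves a ratio unchanged. The anchors give 460/120 = 3.83 and the trial doses 300/100 = 3.00. Put another way, if the anchors are total mg for one patient, matching the start needs a body surface area of 120/100 = 1.20 sm and matching the maximum needs 460/300 = 1.53 sm. One patient cannot have both.

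**Step 2: central curve implied by the anchors.** The article says that log α is the log-odds of toxicity at the reference dose. The standardised dose must then be zero there, which points to the log of the dose ratio. With logit(0.10) = −2.1972 and logit(0.25) = −1.0986:

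- Printed anchors: slope = 1.0986 / ln(460/120) = 1.0986 / 1.3437 = 0.8176.
- Anchors at 100 and 300 mg/sm: slope = 1.0986 / ln 3 = 1.00.

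The probability at dose d is expit(−2.1972 + slope × ln(d / lower anchor)). If the anchors are total mg, d is replaced by d × body surface area. Both curves reproduce 10% and 25% at their own anchors.

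**Step 3: results on the Table 2 levels (%).**

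| Dose, mg/sm | Printed anchors as mg/sm | As total mg, 1.5 sm | As total mg, 1.9 sm | Anchors at 100 and 300 mg/sm |
|---|---|---|---|---|
| 100 | 8.7 | 11.8 | 13.9 | 10.0 |
| 135 | 10.9 | 14.6 | 17.1 | 13.0 |
| 155 | 12.0 | 16.0 | 18.8 | 14.7 |
| 180 | 13.4 | 17.7 | 20.7 | 16.7 |
| 200 | 14.4 | 19.0 | 22.2 | 18.2 |
| 235 | 16.1 | 21.1 | 24.5 | 20.7 |
| 270 | 17.7 | 23.1 | 26.7 | 23.1 |
| 300 | 19.0 | 24.7 | 28.4 | 25.0 |

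Worked example, total mg at 1.5 sm and 100 mg/sm: the total dose is 150 mg, ln(150/120) = 0.2231, and expit(−2.1972 + 0.8176 × 0.2231) = expit(−2.0148) = 11.8%.

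**Step 4: direction.** Against the last column, the mg/sm reading is lower by 1.3 points at 100 mg/sm and by 6.0 points at 300 mg/sm. The total-mg reading is higher by 1.8 to 3.9 points at 100 mg/sm. At 300 mg/sm it lies between 0.3 points lower and 3.4 points higher.

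**Step 5: sensitivity to the dose scale.** On linear dose the printed slope is 1.0986/340 = 0.00323 per unit, and the probability is expit(−2.1972 + 0.00323 × (d − 120)). Read as mg/sm, this gives 9.4% at 100 and 16.6% at 300. Read as total mg (150 to 190 mg at the start, 450 to 570 mg at the top), it gives 10.9 to 12.2% and 24.4 to 32.2%. The same dependence on the unit appears.

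These are curves through two points, not the full Bayesian prior.

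**The case against.** The strongest defence is that 120 and 460 were never meant to be trial doses. In mg/sm, 120 is the established PIPAC dose. Section 1.3 says that PIPAC doses were set at about 20% of the HIPEC dose, and 100/460 is 22%. Section 3 says that HIPEC doses are usually higher, and the cisplatin ceiling is itself a HIPEC dose. So 460 may be a HIPEC reference, and anchoring a prior outside the dose ladder is legitimate. On that reading the numerical gap is zero. This is plausible and cannot be excluded, but the article never says it, and it does not make the printed names right.

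A second defence is that the unit is printed as mg. Read so, at 1.53 sm the upper anchor equals the trial maximum and only the lower one is off. This stands too. A reader might infer from the mg/sm column that the prior is too optimistic and favours escalation. The document does not support that inference, because it requires a unit that is not printed and the literal unit gives about the same or higher toxicity.

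Third, no effect on the design is shown. None of the tabulated curves reaches the 33% overdose limit on the Table 2 levels, levels cannot be skipped, and the model is updated after each cohort. The curves do cross the 16% line at different levels (between 200 and 235 mg/sm for the mg/sm reading, between 155 and 180 mg/sm for the 100 and 300 mg/sm anchors). Without the prior variances, that does not establish a different dosing decision. This also stands, and it limits the point to the calibration statement.

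**Conclusion.** The inconsistency is certain: the anchors named as the trial's start and maximum are not its start and maximum, and no unit conversion makes them so. It should be corrected, because the prior feeds the toxicity probability used after every cohort.

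Whether the prior itself is wrong is not established. If the trial's own doses were meant, the central prior toxicity at the top level should be 25%. The printed anchors give 19.0% there if read as mg/sm and 24.7 to 28.4% if read as total mg. At the first level the figures are 10% against 8.7% or 11.8 to 13.9%. If 120 and 460 are intended external references, only the wording is at fault.

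These figures rest on reading the bare 10 as 10%, on the log-dose form, on an assumed body surface area of 1.5 to 1.9 sm for the total-mg reading, and on point anchors. The article does not support a claim that doses will be chosen wrongly.

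**What to change.** State both anchors in mg/sm and both probabilities as percentages. Then take one of two routes:

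- If the anchors are meant to be the trial's own first and last doses, recalibrate the two prior parameters to 10% at 100 mg/sm and 25% at 300 mg/sm, and check the resulting prior on all eight levels of Table 2. The cost is a recalculation and possibly a protocol amendment, since the design has ethics committee and drug agency approval.
- If 120 and 460 are external reference doses, say so, give the source of each, and stop calling them the starting and maximum doses. The cost is one corrected sentence.

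Neither route needs extra patients.
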